## Abstract

**Background and purpose::**

Poststroke cognitive impairment (PSCI) is common, but the impact of β-amyloid (Aβ) on PSCI is uncertain. The proposed study will investigate amyloid pathology in participants with PSCI and how differently their cognition progress according to the amyloid pathology.

**Methods::**

This multicenter study was designed to be prospective and observational based on a projected cohort size of 196 participants with either newly developed cognitive impairment, or rapidly aggravated CI, within 3 months after acute cerebral infarction. They will undergo ^18^F-flutemetamol positron emission tomography at baseline and will be categorized as either amyloid-positive (A+) or amyloid-negative (A−) by visual rating. The primary outcome measures will be based on Korean Mini-Mental State Examination changes (baseline to 12 months) between the A+ and A− groups. The secondary outcome measures will be the dementia-conversion rate and changes in the Korean version of the Montreal Cognitive Assessment (baseline to 12 months) between the A+ and A− groups.

**Conclusions::**

This study will provide a broadened perspective on the impact of Aβ on the cause and outcomes of PSCI in clinical practice. Identifying amyloid pathology in patients with PSCI will help select patients who need more focused treatments such as acetylcholinesterase inhibitors

**Trial registration::**

Clinical Research Information Service identifier: KCT0005086

## Introduction

1

Poststroke cognitive impairment (PSCI) is common, occurs within 3 months after a stroke (or even later), and is associated with poor outcomes.^[1,2]^ The combination of neuroanatomical lesions caused by stroke, other white-matter lesions, and cerebral microbleeds due to small-vessel diseases, and Alzheimer disease (AD) pathologies are known to contribute to PSCI,^[2]^ but our understanding of the role of amyloid pathology in PSCI is still insufficient. Considering a recent comprehensive review,^[3]^ impaired perivascular-space integrity, inflammation, hypoxia, and blood–brain barrier breakdown after stroke can all lead to accelerated deposition of β-amyloid (Aβ) within brain parenchyma and cerebral vessel walls and exacerbations of cerebral amyloid angiopathies. This Aβ deposition in the brain parenchyma would then be the initiating event that leads to synaptic dysfunction and the induction of both cognitive decline and dementia. Despite these proposed Aβ mechanisms, study results for the impact of Aβ on PSCI have been mixed. Several previous reports have supported faster cognitive decline with amyloid pathology in PSCI.^[4–7]^ The results of Mao et al^[7]^ which considered thyroid function in addition to Aβ, indicated positive correlations between Aβ and free thyroxin with PSCI progression, suggesting that these indicators have the potential to predict disease progression and outcome. A 3-year longitudinal study that examined cerebral infarction, hemorrhage, and transient ischemic attack (TIA) reported rapid PSCI progression in amyloid-positive patients.^[4]^ On the other hand, amyloid-pathology prevalence in PSCI was found not to increase in cognitively healthy stroke survivors, suggesting that factors other than amyloid pathology were likely contributors to the development of PSCI.^[8]^ Moreover, Hagberg et al^[9]^ reported that amyloid binding was uncommon and that amyloid deposition did not correlate with cognition in a 7-year longitudinal study. Therefore, this study was designed to examine how cognitive-impairment progression in PSCI is related to amyloid pathology. We will investigate amyloid pathology in patients with PSCI, and compare how differently their cognition progress according to the amyloid pathology.

## Methods

2

### Study design

2.1

This cognitive decline according to amyloid uptake in patients with PSCI study is designed to be a prospective, multicenter, observational, and hospital-based cohort study using patients suffering from cognitive impairment (CI) after acute stroke. Participants diagnosed with either amnestic mild cognitive impairment (MCI)^[10]^ or mild dementia compatible with Diagnostic and Statistical Manual of Mental Disorders-fourth edition criteria^[11]^ after acute cerebral infarction will be consecutively recruited through 11 hospital neurology clinics. The flow chart of the study was shown in Figure 1.

**Figure 1 F1:**
[figure not shown]
Study flow diagram. CDR = clinical dementia rating, GDepS = geriatric depression scale-short form, GDS = global deterioration scale, K-MMSE = Korean version mini-mental state examination, MoCA-K = Korean version Montreal cognitive assessment, PET = positron emission tomography.

### Study registration

2.2

This study trial has been registered on the Clinical Research Information Service (http://cris.nih.go.kr) with an ID of No. KCT0005086).

### Participants

2.3

Participants diagnosed with either amnestic MCI^[10]^ or mild dementia compatible with Diagnostic and Statistical Manual of Mental Disorders-fourth edition criteria^[11]^ after acute cerebral infarction will be consecutively recruited. The participant inclusion criteria will be: age between 60 and 85 years; complaint of newly developed CI or rapidly aggravated CI within 3 months after an acute cerebral infarction; delayed verbal–memory recall scores using either the Seoul Neuropsychological Screening Battery II^[12]^ or the Literacy Independent Cognitive Assessment^[13]^ are below either −1.0 standard deviation or the 16th percentile; and a clinical dementia rating (CDR)^[14]^ score of 0.5 or 1. We will exclude participants diagnosed with dementia previous to the acute infarction; prescribed acetylcholinesterase inhibitors (AChEIs); diagnosed with strategic infarcts or large cortical infarcts; with other neurological, psychological, or metabolic disorders affecting cognition; and with modified Rankin scale^[15]^ scores >3. See Table 1 for details of these inclusion and exclusion criteria.

**Table 1 T1:** Inclusion and exclusion criteria.

Inclusion criteria
(1) Age between 60 and 85 years
(2) Complaint of newly developed CI or rapidly aggravated CI within 3 months after acute cerebral infarction
(3) Delayed-recall scores of verbal memory in SNSB II or LICA were below −1.0 SD or 16th percentile
(4) CDR was 0.5 or 1

Exclusion criteria
(1) Already had dementia before the acute cerebral infarction
(2) Were prescribed an AChEI before the acute cerebral infarction
(3) Were diagnosed with a strategic infarction or a large cortical infarction
(4) Any other neurological, psychological, or metabolic disorders affecting cognition
(5) mRS >3
(6) Any hearing, visual, or severe language impairments (including aphasia) that could prevent efficient evaluation of the patient
(7) Chronic liver disease, or renal disease being considered for dialysis
(8) Any malignancy not confirmed as cured
(9) Schizophrenia or bipolar disorder based on DSM-IV axis I
(10) Mental retardation
(11) History of encephalitis
(12) Any head trauma that could cause loss of conscientiousness at least 1 hour
(13) Any history of cerebral hemorrhage or brain tumor
(14) Abnormal results of thyroid function test
(15) Cerebral dysfunction related to vitamin B12 or folate deficiency
(16) Neurosyphilis
(17) Had a history of metabolic encephalopathy

AChEI = acetylcholinesterase inhibitor, CDR = clinical dementia rating, CI = cognitive impairment, DSM-IV = Diagnostic and Statistical Manual of Mental Disorders-fourth edition, LICA = Literacy Independent Cognitive Assessment, mRS = modified Rankin scale, SD = standard deviation, SNSB=Seoul Neuropsychological Screening Battery.

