#### Assessment measures

2.6.1

For each participant, we will collect basic demographic data (eg, age, sex, years of education), comorbid-disease data that includes vascular risk factors (eg, hypertension, diabetes mellitus, ischemic heart disease, atrial fibrillation, hyperlipidemia, smoking, and alcohol use), medication history, body mass index, and family history of dementia or stroke. All participants will have 3.0-T magnetic resonance imaging (MRI) performed within 1 week of their acute cerebral infarction at the site where it was originally treated. Laboratory tests, including apolipoprotein E genotyping, will be performed before the baseline studies. MRI and MR angiographic imaging resulting from the acute cerebral infarction event will be acquired from each hospital where participants were treated. Included images will be from axial T1-weighted, T2-weighted, T2-weighted fluid-attenuated inversion recovery, diffusion-weighted, gradient-recalled echo, susceptibility-weighted, and coronal T1 sequence imaging, as well as images of intracerebral and extracerebral vessels. We will investigate the location and size of each acute cerebral infarction. We will also evaluate the degree/level of white-matter hyperintensities, the number of lacunes, the number of microbleeds, and the grade of medial-temporal atrophy. For evaluation discrepancies, these will be resolved by investigator consensus. Patient stroke-severity will be assessed at admission using the National Institute of Health Stroke Scale,^[16]^ and the modified Rankin scale. For each patient, we will additionally determine a Hachinski ischemic score^[17]^ and a Trial of ORG 10172 in Acute Stroke Treatment classification^[18]^ for stroke workup.

We will use the informant questionnaire on the cognitive decline in the elderly (IQCODE)^[19]^ to compare a patient's performance after acute infarction with that before the infarction using the information provided by a patient's caregiver. To evaluate participant cognition, we will perform baseline assessments using the Korean Mini-Mental State Examination (K-MMSE),^[20]^ the Korean version of the Montreal Cognitive Assessment (MoCA-K),^[21]^ the CDR, the Global Deterioration Scale,^[22]^ the Korean Instrumental Activities of Daily Living,^[23]^ the Geriatric Depression Scale-short form,^[24]^ and the Literacy Independent Cognitive Assessments or the Seoul Neuropsychological Screening Battery assessments.

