### Statistical analysis

2.9

We will either apply independent *t* tests for normally distributed continuous variables, the Mann–Whiney *U* test for non-normally distributed variables, or a chi-squared test for categorical variables to compare the 2 participant groups. Linear mixed models will be used to compare any changes in K-MMSE and MoCA-K scores between the A− and A+ groups with age, sex, and education as covariates. A chi-squared test will be used to compare conversion-to-dementia prevalence between the A− and A+ MCI groups, but Fisher exact test will be used if >20% of the values are <5.

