## Discussion

3

Although PSCI occurs frequently in patients with stroke, its prevalence and underlying mechanisms have not been studied in detail. In addition, as a variety of factors are known to contribute to PSCI, it is unclear if Aβ is a predictor of its progression or poststroke dementia, even though Aβ positivity is known to be a strong predictor of progression or conversion to AD from MCI.^[25–27]^ Previous studies of the prevalence of Aβ in PSCI and its effect on the prognosis of PSCI were limited because patients were enrolled even though they underwent initial neuropsychological testing 3 to 6 months after their stroke events, patients with pre-existing dementia were not clearly excluded, cohorts were small, patient assessments were made using computerized tomography results without MRI, a variety of stroke etiologies were used (eg, TIA, hemorrhage, and infarction), and over half of the studies used Pittsburgh compound B as an investigative amyloid tracer, which was not approved for clinical practice.^[4,8,9,28,29]^ Because of these limitations, there is no consensus yet regarding the contribution of Aβ to PSCI and the impact of Aβ on the PSCI prognosis. We hypothesized that Aβ deposition may accelerate neuroinflammation related to stroke, which in turn could result in rapid PSCI progression. With this in mind, we aimed to determine if Aβ affects PSCI cognitive decline. Similar to other studies, the present design also has a limited number of participants and a limited observation period, but the present proposed study overcomes other limitations. In particular, we have tried to register more homogenous groups to find out whether the pathology of AD could contribute to cognition after cerebral infarction. Its strengths are the enrollment of PSCI participants only with acute cerebral infarction (no cerebral hemorrhage or TIA considering that these have different mechanisms and clinical outcomes compared to infarction), the exclusion of strategic infarction or large cortical infarction where the lesions themselves would play a too critical role in cognitive functions or show too much lesion-specific CI, the enrollment of participants who have neuropsychological test results within 3 months of acute infarction, the acquisition and analysis of 3.0-T MRI data, and the use of ^18^F-FTM as the amyloid tracer which is approved for clinical practice.

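### The 3-month limit in Table 1 dates the complaint, not the testing that the Discussion claims, and the stroke-to-baseline interval is neither bounded nor among the stated model covariates

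*Protocol article*

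**What the plan says.** **Entry rule.** Inclusion criterion 2 in Table 1 (section 2.3) reads "2) Complaint of newly developed CI or rapidly aggravated CI within 3 months after acute cerebral infarction", and the running text of 2.3 ties the 3 months to the complaint in the same way. Criterion 3 sets a memory threshold without a date: "3) Delayed-recall scores of verbal memory in SNSB II or LICA were below −1.0 SD or 16th percentile". Criterion 4, on CDR, has no date either.

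**Baseline.** Section 2.6.1 says "we will perform baseline assessments using the Korean Mini-Mental State Examination (K-MMSE" and lists the other scales, with no interval from the stroke. The same section does tie the MRI to the stroke: "performed within 1 week of their acute cerebral infarction".

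**Claim.** The Discussion faults earlier work because "patients were enrolled even though they underwent initial neuropsychological testing 3 to 6 months after their stroke events", and names as a strength of this study "the enrollment of participants who have neuropsychological test results within 3 months of acute infarction".

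**Outcome and model.** Section 2.7 makes the primary outcome the K-MMSE change from baseline to week 52, A+ against A−. Follow-up tests are at 6 and 12 months (section 2.6). Section 2.9 compares the changes by linear mixed models "with age, sex, and education as covariates".

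**The concern.** There are two separate points.

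The first is a conflict in the text. The study is presented as avoiding first testing at 3 to 6 months, but its rules admit a patient who complains in month 3 and is tested in month 5. A reader who relies on the Discussion would describe the cohort wrongly.

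The second concerns the primary comparison. Baseline K-MMSE is the zero point of the outcome, and the 52 weeks run from that visit rather than from the stroke. Baseline may fall days or months after the infarction, so the follow-up year covers different stretches of the post-stroke course in different patients. If cognition recovers early after stroke, a patient tested early has more recovery still to come inside the measured change than one tested late.

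Amyloid status is not randomised, so nothing in the design balances the interval between A+ and A−. Criterion 2 also pools newly developed with rapidly aggravated impairment, and section 2.7 plans to relate IQCODE to amyloid positivity. The investigators therefore allow that pre-stroke decline may differ by amyloid status. A difference in time to testing would be a further step; it is plausible but not documented.

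**Working it through.** **1. The texts side by side**

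| Item | Dated from the infarction? |
|---|---|
| Complaint (criterion 2) | Yes, within 3 months |
| Delayed recall (criterion 3) | No |
| CDR (criterion 4) | No |
| Baseline K-MMSE (section 2.6.1) | No |
| MRI (section 2.6.1) | Yes, within 1 week |
| Neuropsychological results (Discussion) | Yes, within 3 months |

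The last row does not follow from the rows above it.

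**2. The plan's own figure**

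Inputs from section 2.8: difference 2, SD of change 5, alpha 0.05, power 80%, 20% discontinuation. A one-sided calculation gives 78 per group, and 78/0.8 = 97.5, rounded to 98, × 2 = 196, as stated. A two-sided calculation gives 99 per group and 248 in total, which does not match. The sample size is not disputed here; the one-sided setting is used below because it reproduces the plan. With 78 completers per group the standard error of the contrast is 5 × √(2/78) = 0.80, and power is 80.3%.

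**3. Recovery still to come at baseline (assumed)**

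The documents give no recovery size or speed. Assume total recovery A = 3 points with half-life h of 4 or 6 weeks. For a baseline at week w, the recovery inside the next 52 weeks is about A × 0.5^(w/h); what remains after that year is negligible.

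| Baseline week | h = 4 | h = 6 |
|---|---|---|
| 1 | 2.52 | 2.67 |
| 4 | 1.50 | 1.89 |
| 8 | 0.75 | 1.19 |
| 12 | 0.37 | 0.75 |
| 20 | 0.09 | 0.30 |

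The week-20 row is 3 × 0.5^5 and 3 × 0.5^(20/6).

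**4. If the interval differs between groups**

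Take one group tested at the earlier week and the other at the later week. The bias is the difference between the two entries.

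| Gap | h = 4 | h = 6 |
|---|---|---|
| Week 1 against 4 | 2.52 − 1.50 = 1.02 | 2.67 − 1.89 = 0.78 |
| Week 4 against 8 | 1.50 − 0.75 = 0.75 | 1.89 − 1.19 = 0.70 |
| Week 8 against 12 | 0.75 − 0.37 = 0.38 | 1.19 − 0.75 = 0.44 |
| Week 9 against 12 | 0.63 − 0.37 = 0.26 | 1.06 − 0.75 = 0.31 |

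A 3 to 4 week gap therefore gives roughly 0.3 to 1 point. A full 4-week gap starting at week 1 with h = 4 goes somewhat above this: 2.52 − 3 × 0.5^(5/4) = 2.52 − 1.26 = 1.26. Every entry is proportional to A, so a 1-point total recovery gives a third of these values. With no gap the bias is zero.

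For scale, a bias of 0.5 point is 0.5/0.80 = 0.62 standard errors. The one-sided type I error rises from 5% to 15.4% if the bias favours the hypothesis. Power falls from 80.3% to 59.0% if it works against it.

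**5. If the interval does not differ between groups**

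Recovery cancels in the contrast and only its spread remains. With baseline uniform over weeks 1 to 12, the same curve adds an SD of 0.60 (h = 4) or 0.55 (h = 6). The SD of change becomes √(25 + 0.60²) = 5.04 or √(25 + 0.55²) = 5.03. Power moves from 80.3% to 79.8% or 79.9%.

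**The case against.** The strongest reply is that the wording mismatch does not itself produce the bias. Under the curve above, a patient tested at month 5 has almost no early recovery left and is the least affected. A 3-month ceiling alone would keep the early baselines and drop the most stable ones. This stands, and it is why the two points are kept apart. A reader might infer that the loose criterion lets early recovery contaminate the primary outcome. The documents do not support that: they contain no recovery data, and recovery common to both groups cancels.

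A reader might also set the spread between a week-1 and a week-12 baseline (about 2 points) beside the planned 2-point difference. That compares two extreme patients with a difference in group means, and is not a measure of bias. Testing in week 1 is also unlikely, since entry needs a diagnosis of MCI or dementia, a memory battery and a CDR through neurology clinics.

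The size of gap needed is a further fair objection. If baselines were uniform over weeks 1 to 12, the SD of the interval would be 11/√12 = 3.2 weeks, so a 3 to 4 week gap in means is about one SD. That is large, and nothing in the documents indicates that it will occur or in which direction.

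Finally, Figure 1 is not shown and might give a baseline window, and a fuller plan might add covariates. If Figure 1 does give a window, Table 1 would still need to agree with it. The covariate list in section 2.9 is stated rather than left open, and it does not contain the interval.

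**Conclusion.** The conflict between Table 1 with section 2.3 and the Discussion is established on the text: the entry rules do not deliver the testing window claimed as a strength. This needs no assumption.

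The statistical point is conditional. The stroke-to-baseline interval is unbounded on both sides and absent from the stated covariates, so the primary contrast could be confounded if the interval differs by amyloid status. The illustrated bias of roughly 0.3 to 1 point rests on three assumptions: the 3-point total recovery, the 4 to 6 week half-life, and a 3 to 4 week difference in group means. It scales with the first and vanishes without the third. If the groups do not differ in timing, about half a percentage point of power is lost, which would not justify a change by itself. The point deserves correction because the remedy is cheap and answers a foreseeable question about the primary result, not because bias has been shown.

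**What to change.** 1. Reword Table 1 and section 2.3 so that the qualifying neuropsychological tests and the baseline K-MMSE are done within 3 months of the infarction, or withdraw the claim from the Discussion.
2. Derive weeks from infarction to baseline K-MMSE and add it, with its interaction with visit, to the primary mixed model in section 2.9. The interaction is the part that matters, because the interval would act on the change and not only on the level. This second step deals with the possible confounding; the first only makes the texts agree.

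**Cost.** One criterion is reworded, and one covariate with its interaction is added from dates the study needs anyway. A few late-tested patients become ineligible, and the model spends a few more parameters.

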### Recruitment

2.4

We will recruit 196 patients with CI after acute cerebral infarction. The researcher will explain the aim and the details of this study and will obtain informed consent from potential participants before the collection of information. Participation in this study will not affect their clinical treatment.

### Intervention

2.5

This is an observational study. No study-related interventions are planned. For MCI patients, regardless of amyloid positivity, they will not be treated with AChEIs, whereas only A+ dementia patients will be treated with AChEIs.

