The K-MMSE, MoCA-K, CDR, Global Deterioration Scale, and Geriatric Depression Scale-short form will be repeated at 6 and 12 months as follow-up assessments.

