### Study outcomes

2.7

The primary outcome measure will be to compare K-MMSE assessment changes (from baseline to week 52) between groups A+ and A− (determined by the visual rating of amyloid PET). The secondary outcome measures will be to compare the A+ and A− groups for differences in the conversion rate to dementia and for changes in MoCA-K assessments (from baseline to week 52). In addition to the clinical factors related to progression, we will investigate the various factors related to amyloid positivity including the IQCODE, as well.

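### The pooled K-MMSE and MoCA-K contrasts mix amyloid status with AChEI treatment in dementia, so they show prognosis under that treatment rule and not, by themselves, the effect of Aβ on decline

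*Protocol article*

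**What the plan says.** **Population.** Section 2.3 enrols patients with amnestic MCI "or mild dementia compatible with Diagnostic and Statistical Manual of Mental Disorders-fourth edition criteria", with a CDR of 0.5 or 1. The AChEI exclusion in Table 1 concerns prescriptions before the infarction, not treatment during follow-up.

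**Treatment.** Section 2.5 calls the study observational and then states the care rule: no AChEI in MCI whatever the amyloid result, "whereas only A+ dementia patients will be treated with AChEIs".

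**Outcome and model.** The primary outcome in 2.7 is to "compare K-MMSE assessment changes (from baseline to week 52) between groups" A+ and A−. MoCA-K change is a secondary outcome on the same footing. Both scores "will be repeated at 6 and 12 months as follow-up assessments" (2.6.1). The mixed models in 2.9 compare the "groups with age, sex, and education as covariates". Only the conversion test is limited by diagnosis: it compares the A− and "A+ MCI groups, but Fisher exact test will be used" when counts are small.

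**Aims.** The Introduction wants to "compare how differently their cognition progress according to the amyloid pathology". The Discussion goes further: "we aimed to determine if Aβ affects PSCI cognitive decline". Its closing paragraph also expects the results to inform standards for AChEI use in PSCI.

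**The concern.** The drug is given according to the exposure under study. In dementia, A+ patients are treated and A− patients are not, so a difference between them combines amyloid status with AChEI treatment. In MCI, neither group is treated at entry. The planned K-MMSE and MoCA-K contrasts average over these two different comparisons, and no stated term or subgroup keeps them apart.

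The Introduction's question is about the course of cognition by amyloid status, and the pooled contrast answers it for patients managed in this way. The Discussion's question is whether Aβ itself affects decline. For that question, a small pooled difference has two readings: amyloid matters little, or amyloid matters and the drug offsets part of it. The same ambiguity undercuts any inference about who should receive AChEIs, because the drug was never given to a comparable A− group.

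**Working it through.** **1. Who is treated, according to 2.5**

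| Baseline diagnosis | A− | A+ |
|---|---|---|
| MCI | no AChEI | no AChEI at entry |
| Mild dementia | no AChEI | AChEI |

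In the dementia row the treatment indicator equals the amyloid indicator. Over the whole table it equals A+ multiplied by dementia. An AChEI covariate added to the model would therefore be the same variable as the amyloid-by-diagnosis interaction. It could be read as a drug effect only by assuming that the amyloid effect is identical in MCI and dementia.

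**2. What the pooled contrast contains**

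Let d be the extra 12-month K-MMSE loss in A+ without the drug, taken as equal in MCI and dementia. Let f be the share with dementia, taken as equal in both groups, and b the AChEI benefit in points. Then

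pooled difference = (1 − f)·d + f·(d − b) = d − f·b.

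If b is positive, the pooled difference is smaller than d by f·b. The article gives neither f nor b. For scale only, with assumed f = 0.2 to 0.4 and b = 1 to 2 points, the masked amount runs from 0.2 × 1 = 0.2 to 0.4 × 2 = 0.8 points. This is not an estimate for the study.

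**3. The plan's own figure**

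Inputs from 2.8: difference 2, SD of change 5, alpha 0.05, power 80%, discontinuation 20%.

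n per group = 2 × 5² × (1.645 + 0.842)² / 2² = 77.3, rounded up to 78.

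78 / 0.8 = 97.5, rounded up to 98 per group, or 196 in total.

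The stated 78 and 196 reproduce with a one-sided alpha. A two-sided alpha gives 98.1, rounded up to 99 per group. That is a separate matter and plays no part here.

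**4. Precision of an MCI-only K-MMSE estimate**

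Half-width of the 95% CI = 1.96 × 5 × √(2/n), with 78 per group at 12 months, equal groups as in 2.8, and the dementia share assumed to be 20% or 40%.

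| Set | n per group | Half-width (points) |
|---|---|---|
| Pooled | 78 | 1.57 |
| MCI, 20% dementia | 78 × 0.8 ≈ 62 | 1.76 |
| MCI, 40% dementia | 78 × 0.6 ≈ 47 | 2.02 |
| Dementia, 20% | 16 | 3.46 |
| Dementia, 40% | 31 | 2.49 |

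These are simple two-sample intervals; the mixed model may differ somewhat. The article gives no SD for MoCA-K, so the same calculation cannot be made for it.

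**The case against.** The best defence is that the study is observational and mostly prognostic. The abstract and the Introduction ask how cognition progresses by amyloid status, section 2.4 says that taking part does not alter treatment, and prognosis under a stated care rule is a coherent target. This stands: the pooled contrast is not wrong for that aim and should remain primary.

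A second defence is that a journal article may leave stratified and supportive analyses to a fuller document. This carries less weight here, because 2.9 does state the model and its covariates and does restrict one test to MCI. The difficulty lies between the treatment rule, that model and the wider aim, all of which are stated.

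A reader might go further in three ways, none of which the document supports:

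- **That the study loses power.** Section 2.8 does not say that its 2-point difference is drug-free. If it already describes the contrast under 2.5, no planned power is lost and only interpretation is affected.
- **That more dementia in A+ would bias the contrast away from zero.** No dementia shares or rates of decline by diagnosis are given. The Introduction also treats dementia as a possible consequence of Aβ deposition, so a different diagnosis mix may be part of how A+ patients differ.
- **That the primary contrast should therefore be standardised over baseline diagnosis.** For the same reason this could remove part of the amyloid-related difference. It would also leave the drug term in place.

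**Conclusion.** The point holds as a matter of interpretation. Under 2.5 as written, amyloid status and AChEI treatment cannot be separated within dementia, and the planned K-MMSE and MoCA-K contrasts pool that stratum with MCI. They describe prognosis by amyloid status under the rule. By themselves they cannot settle whether Aβ affects decline, and they cannot support standards for AChEI use.

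If the drug helps, the distortion runs against the hypothesis of faster A+ decline, so a null pooled result could not be read as no Aβ effect. Its size is unknown, since it depends on a dementia share and a drug benefit that the article does not give. The separation problem itself needs no numerical assumption, only that the rule is followed as stated. This is a cheap improvement and not a flaw that invalidates the design.

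**What to change.** Amend the wording of 2.9:

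1. Keep the pooled A+ versus A− contrast as primary, not standardised over diagnosis, and label it as prognosis under the AChEI rule of 2.5.
2. Prespecify a supportive A+ versus A− estimate of K-MMSE and MoCA-K change, with 95% CI, within baseline MCI. Describe both groups as untreated at entry, and note that A+ participants who convert to dementia may then start an AChEI.
3. Report the dementia stratum descriptively, labelled as amyloid plus AChEI versus neither.

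No new visit, measurement or participant is needed, since baseline diagnosis is known at enrolment. The cost is precision. With the assumed 20% to 40% dementia, the MCI half-width for K-MMSE is about as large as the 2-point target, so a null MCI result should be presented as weak evidence. The MCI estimate is not free of treatment either, because of converters. It is still the closest the study can come to the Discussion's question, as it is the only stratum in which both groups start without the drug.
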